### Study population and recruitment

All women seeking treatment for symptomatic POP with uterine descent POP-Q stage 2 or higher will be considered for inclusion in the trial. Patients with co-existing anterior/posterior defects or concomitant incontinence surgery can also be included.

Women with a surgical history for POP, known malignancy or abnormal cervical smears, a desire to preserve fertility, abnormal ultrasound findings of the uterus or ovaries or abnormal uterine bleeding, and contraindication for laparoscopic surgery are excluded from the study. Individuals who are unable to provide informed consent or to complete the testing or data collection are also excluded.

Eligibility is assessed by a gynecologist and/or residents of our hospital. Patients eligible for participation are counselled on the long duration of follow-up that is involved in the study. The risks associated with uterus removal are clearly outlined. Subsequently, women are provided with verbal and written information prior to enrollment, and written informed consent is obtained.

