### Randomization

After signing an informed consent form, patients are randomized in a 1:1 ratio to either LILS or LSC centrally using a computerized random number generated at the moment of inclusion by a non-physician blinded to the women’s history and with no contact with the patients. Randomization will be stratified according to severity of prolapse (POP-Q stage 2, 3, or 4). The details of the series will be withheld from the investigators or to the participating gynecologists and all participants will receive unique study numbers. The subjects will be informed about the allocated operative procedure shortly after the randomization. Those who withdraw after randomization will be treated according to the preference of the gynecologist.

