### Laparoscopic sacrocolpopexy (LSC)

The initial procedure of LSC was performed similarly to the procedures on the vaginal wall, and sutures were applied on the anterior or posterior vaginal wall similar to LILS. In LSC, a rectangular macroporous, monofilament polypropylene mesh was attached to the anterior vaginal wall with four polyglycolic 1–0 sutures. Another rectangular polypropylene mesh was attached to the posterior vaginal wall with four polyglycolic 1–0 sutures. Then, the peritoneum over the sacral promontory will be incised; the right ureter will be identified. The mesh will be tacked from the vaginal vault to the sacral promontory by using 5.3 × 3.7 mm staples to elevate the vaginal stump. The peritoneum will be closed in a manner covering the promontory part of the mesh and with a running suture covering the cervical part of the mesh.

During the same procedure, additional anterior and/or posterior colporrhaphy or incontinence surgery can be performed if necessary, according to the standard procedures of the hospital.

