### Data analysis

The analysis will be performed with the intention to treat, and stratified for severity of prolapse. Patient characteristics will be summarized using descriptive statistics for continuous variables (mean ± standard deviation, minimum, maximum, and sample size) and frequency tables for categorical variables (numbers and percentages). Differences in group means were tested by Student’s *t* test, or Wilcoxon rank-sum test where data failed to follow a normal distribution after testing with the Kolmogorov-Smirnov test for normality. Differences in group proportions were tested using a chi-square test, or a Fisher’s exact test if data were sparse. Subgroup analysis based on body mass index (BMI) (< 24, ≥ 24), presence of concomitant surgical procedures, or prolapse stage (stage 2, stage 3, and stage 4) will be performed to identify the potential indication for each technique. Statistical analysis was performed using SPSS 20 for Windows (IBM Corp., Armonk, NY, USA) with *p* < 0.05 considered as statistically significant.

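### The subgroup by concomitant surgery is worded as surgery performed, which happens after randomization; if its use differs by arm, an indication read from it could reflect selection rather than effect

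*Protocol article*

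**What the plan says.** All references are to the protocol article.

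- **Data analysis** names three subgroup factors and states their purpose. After BMI (cut at 24), it goes on: "presence of concomitant surgical procedures, or prolapse stage (stage 2, stage 3, and stage 4) will be performed to identify the potential indication" of each technique.
- **Laparoscopic sacrocolpopexy (LSC)**, last paragraph: within the same operation, "additional anterior and/or posterior colporrhaphy or incontinence surgery can be performed if necessary", subject to the hospital's standard practice. The LILS section has no counterpart sentence. I read the sentence as covering both arms, but the text does not say so.
- **Study population and recruitment**: "Patients with co-existing anterior/posterior defects or concomitant incontinence surgery can also be included".
- **Randomization**: "Randomization will be stratified according to severity of prolapse (POP-Q stage 2, 3, or 4"). No other stratification factor is named. Patients learn their allocation before the operation: "The subjects will be informed about the allocated operative procedure shortly after the randomization".
- **Data analysis**, tests: t test or Wilcoxon for means; for proportions, "Differences in group proportions were tested using a chi-square test" or Fisher's exact test if data are sparse; significance at p < 0.05.

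**The concern.** A subgroup comparison keeps the protection of randomization only if membership is fixed before allocation or cannot be influenced by it. Presence of concomitant surgery, read literally, is an event in the operating room, and the surgeon necessarily knows which suspension is being done. The variable is also close to the outcome. Anatomical success requires every vaginal site to be at least 1 cm above the hymen, and colporrhaphy acts on the anterior or posterior wall. Surgical time and blood loss, also listed as primary outcomes, would plausibly change with an added procedure.

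The stated purpose raises the stakes. These subgroups are meant to suggest which women should have which technique. That is a claim that the treatment effect differs between levels, and a comparison of the two arms inside one level cannot establish it.

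**Working it through.** **1. When is membership fixed?**

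| Factor | Fixed before allocation? | Randomization stratum? |
|---|---|---|
| BMI (< 24, ≥ 24) | Yes, a patient characteristic | No |
| POP-Q stage (2, 3, 4) | Yes, preoperative examination | Yes |
| Presence of concomitant procedures | Performed during the allocated operation; no section ties it to a plan made beforehand | No |

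Only the third factor is open to selection after randomization.

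**2. How large could the selection bias be?** Illustration; all inputs are assumed except the overall 90% success rate (Sample size and power considerations).

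- 30% of women have a worse prognosis, with 80% success. The others then have (0.90 - 0.30 × 0.80)/0.70 = 94.3%.
- The two techniques are equally effective.
- Success among women with added surgery = (0.30·q_w·0.80 + 0.70·q_b·0.943)/(0.30·q_w + 0.70·q_b), where q_w and q_b are the probabilities of added surgery in worse- and better-prognosis women.

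| q_w / q_b in LILS | q_w / q_b in LSC | Success LILS | Success LSC | False difference |
|---|---|---|---|---|
| 80% / 20% | 80% / 20% | 85.3% | 85.3% | 0 |
| 80% / 20% | 80% / 40% | 85.3% | 87.7% | -2.4 points |
| 80% / 10% | 80% / 40% | 83.2% | 87.7% | -4.5 points |
| 80% / 10% | 50% / 40% | 83.2% | 89.3% | -6.1 points |

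Example, third row: LILS (0.24 × 0.80 + 0.07 × 0.943)/0.31 = 0.832; LSC (0.24 × 0.80 + 0.28 × 0.943)/0.52 = 0.877. The bias comes from unequal use alone. Its sign depends on which arm adds surgery more freely.

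**3. How precise are the levels?**

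- The plan's own inflation: 89 × 1.2 = 106.8, so 107 per group. After 20% loss, 107 × 0.8 = 85.6, about 86 evaluable. I therefore use 86 to 89 per group. (The standard noninferiority formula gives 0.18 × (1.96 + 0.84)²/0.15² ≈ 63, not 89. That is a separate matter on which this point does not depend.)
- Equal split over three stages (assumed): 86/3 = 28.7 and 89/3 = 29.7, so about 28 to 30 per group per stage.
- 95% half-width at 90% success = 1.96 × √(2 × 0.9 × 0.1/n): 15.7 points at n = 28 and 15.2 at n = 30. For halves of 43 to 45 it is 12.7 to 12.4 points. For the whole trial at 86 to 89 it is 9.0 to 8.8 points.

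**4. What could an interaction test detect?** Two equal halves, 89 per group:

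- SE of the interaction = √(2 × 0.18/44.5) = 9.0 points, twice the main-effect SE of √(0.18/89) = 4.5 points.
- Detectable with 80% power: (1.96 + 0.84) × 9.0 ≈ 25 points.
- Power for a 15-point interaction: Φ(15/9.0 - 1.96) ≈ 39%.

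**The case against.** **Much of the need may be known before allocation.** Eligibility mentions co-existing defects and concomitant incontinence surgery. POP-Q staging, and urodynamics for incontinent women, precede surgery. The text shows when added surgery is performed, not when it is decided, so a reader who infers that it is always decided after allocation goes too far. This stands. It makes the remedy easy but does not cure the wording, because nothing links the subgroup to a plan recorded before allocation.

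**Hospital practice governs the added surgery and names no difference between arms.** If use is the same in both arms, the bias is zero, as the first row of the table shows. So the bias is possible, not certain, and a reader should not infer that the indications will be wrong. A reference to standard practice does not, however, ensure equal use by surgeons who know the arm.

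**The absence of an interaction test is not an error in itself.** This is a journal article, and an analysis plan that is not shown may contain one. That stands. What can be said is only that the tests the article names do not match the purpose it states.

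**False-positive counts are easily overstated.** A reader might take seven levels (2 + 2 + 3) at 5% and infer a 30% chance of a false indication, since 1 - 0.95⁷ = 0.302. The article does not lay down seven within-level tests or a rule that turns p < 0.05 into an indication. The figure is also nominal, assumes independence and is not an upper bound. For the success endpoint, Fisher's test in cells of 28 and 43 per group has an actual size of about 0.8% and 1.9% at 90% success. Three stage cells and four half cells then give 1 - 0.992³ × 0.981⁴, about 9 to 10%. I do not rely on the 30%.

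**The consequence is limited.** The main conclusion rests on the overall 95% interval against -15%, the article speaks only of a potential indication, and no noninferiority claim by subgroup is planned. All true. The subgroups still have a stated role in suggesting who should have which technique, and the article does not label them exploratory.

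**Conclusion.** The point holds for one of the three factors. As worded, the concomitant-surgery subgroup is defined by something done after randomization, at the surgeon's discretion, with the arm known, and outside the stratification. If its use differs by arm, a subgroup difference could be selection. Under the assumed rates above, that amounts to about -4.5 to -6 points for techniques that are truly equal, less for a smaller imbalance, and nothing for equal use. These figures show a mechanism; they do not predict this trial's result. BMI and stage are free of this problem.

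For all three factors, two-group tests at p < 0.05 do not show that the effect differs between levels. With an equal split assumed, a stage cell has a half-width of about 15 to 16 points, as wide as the 15-point margin set for the whole trial. Unequal stages would make the smaller cells less precise still. The primary noninferiority conclusion is not affected. The change should be made because it is cheap and the subgroups are meant to inform indications.

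**What to change.** 1. Define the subgroup by the anterior/posterior defect or the incontinence surgery need or plan **recorded before randomization**, taken from the preoperative POP-Q and urodynamic examination. Surgery actually performed can be described by arm, so that any imbalance is visible.
2. For each factor, report the treatment difference with its 95% interval at every level.
3. Base any statement about an indication on a treatment-by-factor interaction, one per factor.
4. Call the subgroup analyses exploratory in place of the present aim of finding an indication.

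Cost: one field on the baseline form and a few lines in the analysis section. For women already randomized, the field can be filled from the preoperative record if the need or plan was documented there. The downside is low power: about 39% for a 15-point interaction with two equal halves, so there will be fewer positive subgroup statements.

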### Ethics

The trial has been approved by the Medical Ethics Committee of Shanghai First Infant and Maternity Hospital and the local ethics committees of the participating centers (KS1513). Prior to randomization, informed consent will be obtained. A Data and Safety Monitoring Board (DSMB) consisting of two surgeons and one methodologist was estimated. The DSMB will perform regular reviews of all study outcomes and adverse event data after every 25 included patients to ensure that there is no difference in rates of complication and recurrence rates in either group. The result of the meeting will be relayed to the Trial Steering Committee. The advice of the DSMB will only be communicated to the sponsor of the trial. The results of the trial will be widely disseminated to patients, health professionals, commissioners, and policy makers. To achieve a wide clinical audience, the trial results will be disseminated at international congresses, and in peer-reviewed scientific journals.

## Discussion

This is a protocol for a randomized trial comparing LILS with LSC for the treatment of POP-Q stage 2 or higher prolapse with regard to perioperative parameters, such as surgical time, blood loss, intraoperative complications, and hospital stay as well as objective and subjective success rate, recurrence of prolapse, functional recovery, quality of life, postoperative complications, sexual functioning, and cost-effectiveness.

LSC has been viewed as the gold standard treatment for women with POP who desire reconstructive surgery [3]. Robust data are available as regards the practice of this procedure and hence provided cumulative information on the technique for treating POP [13]. The exposure of the anterior longitudinal ligament is the first surgical step of LSC. However, for patients with obesity, abdominopelvic adhesions, sigmoid megacolon, or anatomic variation of abdominopelvic organs, the procedure is relatively hazardous and time-consuming. It is in this anatomical area where most of bleeding and ureter injuries occur. LILS allowed skipping the dangers and technical challengers of sacral mesh fixation. Thus, we considered LILS to be suitable for patients who present with difficult access to the promontory [9]. In our previous study, we reported that LILS is an effective and safe method for treating vaginal vault prolapse.

The findings of this trial will contribute to answer the question whether LILS technique is preferable in women with symptomatic uterine prolapse POP-Q stage 2 or higher. If noninferiority in surgical success is found, the comparison of the secondary outcomes will be essential in selecting the preferred strategy.

## Trial status

This trial is ongoing. The study began in March 2016, and the primary follow-up is expected to be completed by March 2018.

## Abbreviations

CRADI-8: Colorectal-Anal Distress Inventory-8
CRAIQ-7: Colorectal-Anal Impact Questionnaire-7
DSMB: Data and Safety Monitoring Board
LILS: Laparoscopic inguinal ligament suspension
LSC: Laparoscopic sacrocolpopexy
PFDI-20: Pelvic Floor Distress Inventory-20
PFIQ-7: Pelvic Floor Impact Questionnaire-7
PGI-I: Patient Global Impression of Improvement Scale
PISQ-12: Pelvic Organ Prolapse/Urinary Incontinence Sexual Questionnaire-12
POP: Pelvic organ prolapse
POPDI-6: Pelvic Organ Prolapse Distress Inventory-6
POPIQ-7: Pelvic Organ Prolapse Impact Questionnaire-7
RI-10: Recovery Index-10
UDI-6: Urinary Distress Inventory-6
UIQ-7: Urinary Impact Questionnaire-7
